Thus far this research has been relatively limited to ‘Western’ contexts. This study aims to extend this research on grammatical gender and to test whether masculine generics in other language families, specifically Arabic, behave similarly to Indo-European languages. Arabic is one of the most spoken languages around the world, and yet research on the processing of Arabic grammatical gender remains relatively understudied. Additionally, the use of masculine generics in Arabic speaking countries, especially in the context of job recruitment and formal settings, is largely unquestioned and widely accepted as equally representative of all genders. However, a recent study on the language used in Egyptian job recruitment and advertising showed an overuse and inconsistent use of masculine generics, where stereotypically male-dominated industries used masculine generics and stereotypically female-dominated jobs were advertised in feminine grammatical gender regardless of the gender targeted for the role [11]. Additionally, the study showed that jobs were advertised in both singular (majority) and plural masculine generics, and so a key aspect of this investigation is to determine whether masculine generics in singular or plural are interpreted more or less strongly as male-referring. Therefore, the overall aim of this study is to explore how the presence or absence of grammatical gender affects gender representation in perception.

Specifically, the primary objective of this study is to investigate the role that morphological gender marking plays in either entrenching or perhaps mitigating these segregated and polarised recruitment patterns. To do so, we explore the following questions:

1. How does grammatical gender mediate referent expectations in the presence of competing social information?
a. Do singular masculine generics create a male bias in perception, and are these biases different in singular and plural masculine generics?b. Do participants rely more on stereotypical social information or grammatical information to inform their occupational expectations?c. If the social and grammatical cues conflict, do participants exhibit processing costs? Or is there a processing benefit to having congruent social and grammatical cues? And are these benefits or costs consistent across different gender and cue-type combinations?

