Additionally, a secondary objective of the study is to develop an understanding as to what kind of language is more likely to promote the retrieval and use of feminine-inflected words and provide a more gender-inclusive interpretation of language. Here we shift our focus to explore the effect of gender-inclusive and gender-neutral language on occupational expectations. To do so, we experimentally test the potential value of using gender-inclusive language as an alternative to default masculine generics to increase women’s representation in cognition by exploring the following questions:

2. Can gender-fair language mitigate gendered expectations and increase the representation of gender minorities?3. Is gender-neutral language interpreted as such? Specifically, do social gender biases and stereotypes persist, in English, despite the absence of grammatical gender marking?

The third and final aim is to explore some of these effects from a bilingual perspective. Here the study explores whether a subsample of Egyptian bilingual participants exhibit any grammatical gender carry over effects from Arabic in their processing of English gender-neutral language. To do so, we explore the following question:

4. Do English monolinguals and Egyptian bilinguals differ in their gender expectations and reliance on stereotypical information? If yes, do Egyptian Arabic/English bilinguals show effects of transferring their knowledge of Arabic grammatical gender to English?

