### Design

The experiment employs both between and within variation and is randomised through a block design (5 blocks). The first factor, which varies between participants, is the language condition. There are four main language conditions, and one sub-condition: singular masculine generics, singular feminine g- gender, gender inclusive binomial word-pairs, English gender neutral, and plural masculine generics as the sub-condition (see Table 1).

**Table 1 pone.0292936.t001:** Between variation and breakdown of conditions.

Condition		Example
**1.**	Singular generic masculine	مدرس ‘Teacher[+masc]’
**1.1**	Plural generic masculine	مدرسين ‘Teachers[+masc]’
**2**	Singular feminine	مدرسة ‘Teacher[+fem]’
**3**	Gender-inclusive: Feminine/Masculine word-pair	مدرسة/ مدرس ‘Teacher[+fem]/Teacher[+masc]’
**4**	Gender-neutral: English neutral	Teacher

There is one factor that varies within-participant and that is the ‘stereotypicality’ of the role. Role nouns can be associated with men (e.g., *manager*), associated with women (e.g., *nurse*), or neutral (e.g., *student*). All participants are presented with the same 12 role nouns (4 in each stereotype) but in different language conditions.

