### Sampling & participant recruitment

#### Sample characteristics

There are three types of participants that will be recruited for the study: ‘native’ Egyptian Arabic speakers, monolingual British English speakers, and Egyptian bilinguals with ‘native level’ proficiency in both English and Arabic. Fig 1 presents the possible blocks that different participants can be allocated to depending on their characteristics. For all Arabic blocks, Arabic speakers residing in or who have previously resided in Egypt for at least 10 years will be recruited. All other Arabic-speaking countries will be excluded, this is largely because the norming and stereo-typicality of the stimuli is based on an Egyptian sample and so the ecological validity of these categories has not been tested in other Arabic-speaking settings. However, this is not expected to affect the generalisability of the results as the classifications of these roles are likely to be regionally consistent.

Regardless of language spoken, the study will be targeting a gender-balanced sample of participants aged 18 and above. There will be no restrictions placed on age, but age will be included in the mixed effects model as a potential moderating factor.

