## Pre-specified analysis plan

The study uses mixed effects regression, modelled in STATA, to account for within and between variation in the experiment. There are two different outcome categories and therefore multiple models will be used to explore the effect of language on the dependent variables outlined above.

The first set of models related to fluency will utilise linear-mixed-effects models, and models related to gender expectations will use generalised linear mixed effects models for categorical dependent variables. In both cases, the language condition will be defined as the fixed effect. The models will include random slopes for this fixed effect as some occupations may be more affected by the language condition than others. By-participant random slopes and intercepts will be included in the models as random effects. This is because participant variation is expected due to differences in demographic information (age and gender), attitudes towards women (from the exit survey), language dominance measures (exit survey), and participant’s nationality (note that this is likely corelated with attitudes towards women, and highly correlated with language dominance measures). Similarly, by-item random slopes and intercepts will be included as variation due to length of stimuli or familiarity with different occupations should be accounted for.

Interaction effects will be explored between stereotype and language condition, and for a subsample of the data interactions between number and stereotype will also be explored. Interaction effects related to number will help assess the mediating effect of number on gender expectations in masculine grammatical gender.

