### Data processing & cleaning

In this section we describe how we handle outliers, missing data, and model specification. Firstly, given the presence of by-item and by-participant slopes and intercepts, outliers are less likely to be problematic for the analysis. However, as an additional check, using the *extremes* command on STATA for all numeric outcomes (i.e., fluency measures) we will initially check for cases with extremely high or low values. If any extreme values are identified, they will be investigated further by checking their residuals and leverage. A sensitivity analysis will be conducted to determine whether outlier data will be included or excluded in the analysis. If results are heavily affected by the inclusion of an outlier (and there is no evidence to suggest that differences in results are not random) then this data will be excluded from the analysis.

Secondly, if there is more than 5% of the data missing, this will be further investigated to check if by-item attrition is systematic or randomly distributed. If it is randomly distributed, then these missing observations are automatically removed by STATA in analysis. However, if the missing observations are systematic (e.g., most of the missing data is in response to one particular occupation or stimuli) then this will be investigated further and potentially dropped from the analysis.

Finally, to avoid an overspecification of the models, models that include interactions as predictors will be compared to a simplified model that excludes these interactions using the Bayesian Information Criterion (BIC). The BIC will be used to determine if the unrestricted or restricted model is a better fit for the data.

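### Stereotype is not declared as a fixed effect and enters only through an exploratory interaction that BIC may remove, so the answers to questions 3 and 1b depend on a fit criterion

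*Protocol article*

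**What the plan says.** For both the fluency and the gender-expectation models, the Protocol article (Pre-specified analysis plan) says that "the language condition will be defined as the fixed effect". Stereotype is mentioned later in that section: "Interaction effects will be explored between stereotype and language condition". Under Data processing & cleaning, "models that include interactions as predictors will be compared to a simplified model that excludes these interactions" by BIC, and BIC decides which of the two is used.

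The Design section gives stereotype a larger role: "There is one factor that varies within-participant and that is the ‘stereotypicality’ of the role". It adds: "All participants are presented with the same 12 role nouns (4 in each stereotype) but in different language conditions".

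Two research questions in the Introduction turn on stereotype. Question 3 asks: "do social gender biases and stereotypes persist, in English, despite the absence of grammatical gender marking". Question 1b asks: "Do participants rely more on stereotypical social information or grammatical information to inform their occupational expectations".

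The Hypotheses section offers one check for English. If stereotypes drive the answers there, the language effects of conditions 3 and 4 are expected not to differ significantly.

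**The concern.** Question 3 concerns a difference between role classes inside one language condition. Language does not vary in the English block, so a language effect carries no information on it. Question 1b compares two effects, and only one of them is declared as a fixed effect.

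Each noun belongs to one stereotype class. In a model without a stereotype term, the class difference passes into the by-item random intercepts and slopes, which the plan justifies by stimulus length and familiarity. The effect of interest would then be treated as item noise.

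At stake is whether a part of the primary objective (1b) and a secondary question (3) receive an estimate at all, or receive one averaged over conditions in which the plan predicts no stereotype effect.

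**Working it through.** **Inputs.** Sample size section: 30 participants in each of blocks 1–4 and 30 + 30 in the English block. Total 4 × 30 + 30 + 30 = 180, as the plan states. With 12 nouns each, 180 × 12 = 2,160 trials. Counting cells in Tables 2–4:

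| Condition | Trials |
|---|---|
| Masculine | 360 singular + 180 plural = 540 |
| Feminine | 360 + 120 = 480 |
| Word-pair | 360 + 60 = 420 |
| English | 60 × 12 = 720 |

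**Step 1: what each model can estimate** (four conditions by three stereotype classes).
- Language only: the male-minus-female role contrast within English is identically zero and cannot be tested.
- Language + stereotype: estimable, but as one effect common to all conditions.
- Language × stereotype with main effects: full rank (12 of 12 columns; 15 of 15 with the plural as a fifth condition). The contrast within English is estimable.

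**Step 2: what BIC requires.** The interaction has (4 − 1) × (3 − 1) = 6 df. BIC keeps it only if the likelihood-ratio chi-square exceeds 6 × ln(N).
- N = 180 participants: 6 × 5.193 = 31.2 (p about 2 × 10⁻⁵).
- N = 2,160 trials: 6 × 7.678 = 46.1 (p about 3 × 10⁻⁸).

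The plan does not say which N applies, so both are shown.

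**Step 3: what that means for English.** Illustrative assumptions: 90% male answers in the masculine condition and 10% in the feminine, whatever the role; English centred on 50%; the word-pair stereotype effect anywhere from none to the full English effect; clustering ignored. Suppose a true 20-point difference in English (60% v 40%, 240 trials each).
- Direct contrast: z = 0.20 / √(0.24/240 + 0.24/240) = 0.20 / 0.0447 = 4.5.
- Expected interaction chi-square over the additive logistic model: about 7 to 10, against 31 to 46 needed. BIC drops it.

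Solving for the difference at which the expected chi-square equals the threshold gives about 35 to 42 points at N = 180 and 42 to 50 points at N = 2,160, depending on the word-pair effect.

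**Step 4: what is left after dropping.** If the simplified model has no stereotype term, nothing is left for question 3. If a stereotype main effect is kept, it is a weighted average. With no effect in the masculine and feminine conditions, as the Hypotheses section predicts, its share of the English effect is
- 720 / 2,160 = 33% with no word-pair effect;
- (720 + 420) / 2,160 = 53% with a full word-pair effect.

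A 60-point English difference would appear as about 20 to 32 points. A weighted linear fit that allows for the imbalance in block 4 gives 33% to 52%.

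**Step 5: the condition 3 v 4 check.** Similar average language effects are expected if stereotypes drive both conditions. They are equally expected if stereotypes drive neither and both give balanced answers. A non-significant difference therefore cannot show that stereotypes persist in English.

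**The case against.** A reader might infer that questions 3 and 1b have no stated test. The documents do not support that. The plan states the stereotype by language interaction, and once fitted, that model yields the stereotype effect within English and within each Arabic condition. The Outcomes section also derives a variable for whether the expectation agrees with the role's stereotype. Its level in English bears on question 3, and its variation across conditions bears on 1b. This is only a partial route, because no reference value is given and agreement is not defined for neutral roles.

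Nor is the fixed-effect sentence a full list of model terms: under Sample characteristics, "age will be included in the mixed effects model as a potential moderating factor". The predictions are also set out by stereotype within each condition, and the study is divided into components, so English might be modelled alone. Exact contrasts are detail that a condensed article may leave to a fuller plan.

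These points stand, and they limit the finding. They do not remove it, because what the article does fix works against the two questions: the declared fixed effect omits stereotype, BIC may discard the only term that carries it, and the stated English check cannot distinguish the explanations. The dilution figure applies only if a pooled main effect survives, which the text does not say.

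**Conclusion.** The point holds in limited form and is worth correcting before analysis. The plan contains a model that can answer both questions, but whether that model is used rests on a criterion requiring a chi-square of 31 to 46 on 6 df.

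The 35-to-50-point range rests on the assumed 90%/10% answer rates, the unstated N, independent trials and a simplified model that keeps a stereotype main effect. If that model has language only, the comparison has 8 df and thresholds of 8 × ln(N) = 41.5 to 61.4. Smaller differences, from roughly 24 to 35 points depending on N and the word-pair effect, then suffice to keep the stereotype terms, but nothing is left if they are dropped. Clustering by participant and by noun (four nouns per class) would lower both the z of 4.5 and the interaction chi-square. The 33% to 53% share is a linear-scale approximation to models that will be generalised linear.

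**What to change.** In the Pre-specified analysis plan, declare language condition, stereotype class and their interaction as fixed effects in the gender-expectation models. State that they are kept regardless of the BIC comparison under Data processing & cleaning.

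Then name the deciding contrasts, each with a confidence interval:
- **Question 3:** the male-minus-female role contrast within condition 4, separately for monolinguals and bilinguals. This replaces reliance on a non-significant difference between conditions 3 and 4.
- **Question 1b:** the masculine-minus-feminine form contrast set against the male-minus-female role contrast, both within blocks 1–3.

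The cost is a few sentences and no new data. The small downside is a model with more parameters.

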### Conditions

This study can be broken down into three components that help explain experimental blocks and condition allocation in the proposed design. For a detailed breakdown of how participants will be allocated to different blocks based on their characteristics, see Fig 1.

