**Fig 1 pone.0292936.g001:**
[figure not shown]
Condition allocation based on participants’ characteristics.

The first component evaluates the effect of Arabic grammatical gender (in the singular) on occupational expectations amongst Egyptian Arabic speakers. In this component, participants are randomly allocated across blocks 1–3 where they are presented with role nouns that vary by language and stereotype condition through a Latin square (see Table 2). Based on this design, 3 different participants are required to complete an observation for one role noun (e.g., *nurse*) in the masculine, feminine, and word-pair conditions. There are several reasons for this choice; firstly, it reduces the chance that participants develop an intuition about the real purpose of the experiment. Secondly, it prevents participants from anticipating the G-gender of the stimuli. Thirdly, this design helps avoid responses that are strictly based on priming patterns and local syntactic consistency [32].

**Table 2 pone.0292936.t002:** Latin square blocks for the singular Arabic conditions.

Block	Male Stereotype	Female Stereotype	No Stereotype
**Block 1**	مدير Manager [+ masc]	ممرضة Nurse [+ fem]	تلميذة/تلميذ Student [+ fem/masc]
	مهندسة/مهندس Engineer [+ fem/masc]	راقص Dancer [+ masc]	مغنية Singer [+ fem]
	محامية Lawyer [+ fem]	مضيفة/مضيف طيران Flight Attendant [+ fem/masc]	ممثل Actor [+ masc]
	دكتور Doctor [+ masc]	عاملة نظافة Cleaner [+ fem]	مسؤولة / مسؤول مبيعات Salesperson [+ fem/masc]
**Block 2**	مديرة/مدير Manager [+ fem/masc]	ممرض Nurse [+ masc]	تلميذة Student [+ fem]
	مهندسة Engineer [+ fem]	راقصة/راقص Dancer [+ fem/masc]	مغني Singer [+ masc]
	محامي Lawyer [+ masc]	مضيفة طيران Flight Attendant [+ fem]	ممثلة/ممثل Actor [+ fem/masc]
	دكتورة / دكتور Doctor [+ fem/masc]	عامل نظافة Cleaner [+masc]	مسؤولة مبيعات Salesperson [+ fem]
**Block 3**	مديرة Manager [+ fem]	ممرضة/ممرض Nurse [+ fem/masc]	تلميذ Student [+ masc]
	مهندس Engineer [+ masc]	راقصة Dancer [+ fem]	مغنية/مغني Singer [+ fem/masc]
	محامية/محامي Lawyer [+ fem/masc]	مضيف طيران Flight Attendant [+ masc]	ممثلة Actor [+ fem]
	دكتورة Doctor [+ fem]	عاملة/عامل نظافة Cleaner [+ fem/masc]	مسؤول مبيعات Salesperson [+ masc]

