The second component is considered an exploratory sub-experiment of the first which evaluates the effect of plural masculine generics on the occupational expectations of Egyptian Arabic speakers. The key difference between this component and the former is that this block does not test this relationship in other language conditions (such as feminine plurals or in binomial word-pairs) which would require 3 additional blocks instead of one. This component will be used to explore one key question: do plural masculine generics and singular masculine generics elicit the same male-bias in representation? Importantly, this exploratory sub-experiment has 6 experimental stimuli (in the masculine) compared to the other blocks (see Table 3). This is to ensure a balance of masculine and feminine priming throughout the experiment.

**Table 3 pone.0292936.t003:** Experimental block for the plural masculines.

Block	Male Stereotype	Female Stereotype	No Stereotype
**Block 4**	**مديرين** **Managers [+ masc]**	راقصة Dancer [+ fem]	تلميذة/تلميذ Student [+ fem/masc]
	محامية/محامي Lawyer [+ fem/masc]	**ممرضين** **Nurses [+ masc]**	مسؤولة مبيعات Salesperson [+ fem]
	دكتورة Doctor [+ fem]	**مضيفين طيران** **Flight Attendants [+ masc]**	**ممثلين** **Actors [+ masc]**
	**مهندسين** **Engineers [+ masc]**	عاملة نظافة Cleaner [+ fem]	**مغنيين** **Singers [+ masc]**

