The third component explores the effect of an absence of grammatical gender on occupational expectations in a gender-neutral language (English). In this component Egyptian bilinguals and British English monolinguals will complete the experimental task with English stimuli (see Table 4). This component will also be used to explore differences between the occupational expectations of English monolinguals and Egyptian bilinguals. The presence of the English monolingual participants acts as a ‘control group’ for the experiment as they cannot be influenced by G-gender information. All their responses should be driven by their stereotypical expectations of the role nouns presented. On the other hand, the bilingual Arabic/English speaker is expected to behave differently. Bilinguals have been shown to shift their perception of gender by language [8, 33]. In the absence of grammatical gender information, the design may allow us to directly access participants occupational expectations based on social gender. However, participants may also showcase gender ‘carryover effects’ from Arabic grammatical gender instead of relying on social stereotypes. This could be seen in instances where participants consistently describe the referent using masculine morphosyntax (e.g., ‘he’, ‘him’, ‘his’), even when the role stereotype is associated with women (e.g., describing a male nurse, secretary, or dancer), due to the Arabic masculine generic convention.

**Table 4 pone.0292936.t004:** Experimental block for English gender-neutral condition.

Block	Male Stereotype	Female Stereotype	No Stereotype
**Block 5**	Manager	Nurse	Student
	Engineer	Dancer	Singer
	Lawyer	Cleaner	Salesperson
	Doctor	Flight Attendant	Actor

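### By-participant language slopes are specified, yet no participant sees both sides of the English–Arabic or the singular–plural contrast

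*Protocol article*

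**What the plan says.** The Pre-specified analysis plan section of the protocol article makes language condition the fixed effect and gives it random slopes. It then states "By-participant random slopes and intercepts will be included in the models as random effects", and for nouns that "by-item random slopes and intercepts will be included as variation due to length of stimuli". It names no covariance structure and does not fix the data set for each model.

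The Design section says "There are four main language conditions, and one sub-condition", which makes five levels, and "The first factor, which varies between participants, is the language condition". For the first component, however, the Conditions section says "participants are randomly allocated across blocks 1–3 where they are presented with role nouns that vary by language and stereotype condition through a Latin square", so those participants meet three language forms each. Of the plural block (block 4) it says "this block does not test this relationship in other language conditions", meaning feminine plurals and plural pairs. Of block 5 it says that bilinguals and monolinguals "will complete the experimental task with English stimuli".

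Two planned contrasts cross these blocks. The Hypotheses section expects the language effect not to differ between conditions 3 and 4 if stereotype drives responses, which puts Arabic and English in one comparison. The analysis plan also examines number by stereotype in a subsample.

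**The concern.** A by-participant slope describes how an effect differs from person to person. It can be learned only from people observed at both levels. If nobody is, the slope variance either has no information behind it or absorbs something else, here a difference in spread between separate groups of people.

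The fitted random effects set the standard errors of the language contrasts. If the stated structure fails to converge, someone must choose which terms to remove. The BIC rule under Data processing & cleaning covers interactions only and gives no order for random effects. The Design section's description of language as between participants adds to the uncertainty, because taken literally it would rule out any by-participant language slope, including those that blocks 1–3 do support.

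**Working it through.** **Sample size.** The plan's figure reproduces: 4 × 30 + 30 + 30 = 180. I take one block per participant, as this total implies (Fig 1 is not available).

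**Forms seen per participant, counted from Tables 2–4**

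| Block | Singular masc. | Plural masc. | Feminine | Pair | English | Participants |
|---|---|---|---|---|---|---|
| 1–3 | 4 | 0 | 4 | 4 | 0 | 90 |
| 4 | 0 | 6 | 4 | 2 | 0 | 30 |
| 5 | 0 | 0 | 0 | 0 | 12 | 60 |

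**Participants seeing both levels of a pair.** Singular and plural masculine: 0. English with any Arabic form: 0. Singular masculine with feminine or pair: 90. Plural masculine with feminine or pair: 30. Feminine with pair: 90 + 30 = 120.

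**Identification with freely correlated slopes.** Five levels give 5 × 6 / 2 = 15 variances and covariances, plus the residual, so 16 parameters. The rank is that of the derivative of the participant-level covariance matrix with respect to these parameters.

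| Data and levels | Parameters | Rank | Unidentified |
|---|---|---|---|
| All blocks, five levels | 16 | 11 | 5 |
| All blocks, masculine merged over number | 11 | 8 | 3 |
| Arabic blocks 1–4, four levels | 11 | 10 | 1 |
| Singular and plural masculine trials only | 4 | 3 | 1 |
| Blocks 1–3, three levels | 7 | 7 | 0 |

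The five missing terms in the first row are singular with plural masculine, and English with each of the four Arabic forms (1 + 4 = 5).

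**Do the missing terms affect the fit?** On data simulated for 180 participants (level variances 1, covariances 0.5, residual variance 1, all assumed), the log-likelihood stayed at −1429.740 as the never-observed covariances moved from 0 to 0.7. Changing an observed one (singular masculine with feminine, 0.5 to 0.8) lowered it to −1434.397.

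**Independent slopes.** All blocks with five levels now give 6 parameters and rank 6, so the model is identified. Write ω0 for the intercept variance. With dummy coding, ω0 is both the variance at the reference level and the covariance between any two forms. With English as reference, English participants' variance is forced to equal the covariance between Arabic forms. With feminine as reference, the feminine variance is forced to equal it instead. These are different models.

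For the size, I took the best-fitting independent-slope model under the assumed true variances, without noun effects, and compared its standard error for pair v English with the correct one:

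true level = 2 × [1 − Φ(1.96 × model SE / true SE)]

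| Assumed variance of English participants | Reference | Model SE | True SE | True level |
|---|---|---|---|---|
| 1 | English | 0.1605 | 0.1700 | 6.4% |
| 1 | Feminine | 0.1786 | 0.1701 | 4.0% |
| 0.5 | Feminine | 0.1578 | 0.1435 | 3.1% |
| 1.5 | English | 0.1749 | 0.1930 | 7.6% |

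The range is about 3% to 7.5% for this contrast. Other contrasts in the same fit move by other amounts, some larger; I claim no size for them.

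**The case against.** The best reply is that the article does not fix the model closely enough to be called unidentified. The sentence on by-participant slopes names no slope variable, and stereotype, which every participant sees at all three levels, is possible. Several models are foreseen, number is examined in a subsample, and the Conditions section says "This study can be broken down into three components". With independent slopes, or in blocks 1–3 alone, every parameter is identified. Covariance structure and reduction order are also details that a full plan may hold.

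Much of this stands, and it rules out stronger readings that a reader might infer:

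- *That the model cannot be fitted and leaves the language effects undefined.* The unidentified covariances do not enter the likelihood of any observed data. The realistic trouble is non-convergence or unusable variance output.
- *That the model must be cut down after the data are seen.* The gap is visible in Tables 2–4 and can be closed now.
- *That the masculine v feminine test will be badly inflated through lost noun slopes.* The plan commits to by-item slopes, and every noun appears in both forms in blocks 1–3.
- *That block 4's feminine and pair trials distort conditions 2 and 3.* No section says that they are pooled with them.

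The reply does not remove the point. Language is the only slope variable that the section names. The condition 3 v 4 comparison requires a model spanning Arabic and English. With free correlations, the number comparison is deficient even in its own subsample. The Design section's description of language contradicts Table 2 under any covariance structure.

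**Conclusion.** The point holds in limited form. The stated random-effects structure asks for within-person slopes for English v Arabic and for number, and this design cannot supply them. With freely correlated five-level slopes, 5 of 16 parameters are unidentified. With independent slopes, the English slope variance only absorbs a difference in between-participant variance, and the standard errors shift modestly with the reference level: about 3% to 7.5% true level for a nominal 5% test of pair v English.

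The counts and ranks rest on Tables 2–4 and one block per participant. The percentages rest on assumed variances and could be smaller or larger. The point also takes language as the slope variable, which is the natural reading though not an explicit statement. It is a correction worth making before the analysis, and it does not invalidate the study.

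**What to change.** In the Design section, say that singular masculine, feminine and pair vary within participant in blocks 1–3, while number and English v Arabic vary between participants.

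In the Pre-specified analysis plan section:

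- State for each model which blocks it uses and which covariance structure applies.
- Limit by-participant language slopes to masculine, feminine and pair in blocks 1–3, where freely correlated slopes are identified (7 parameters, rank 7).
- Treat number and English v Arabic as between-participant fixed effects, with by-participant intercepts, no by-participant slope, and a participant variance allowed to differ by group.
- Keep by-noun slopes where the nouns support them; for number, these are the six nouns shown in the plural.
- Keep the condition 3 v 4 comparison as a between-participant contrast. It need not become merely descriptive.
- Give the order in which random effects are simplified if a model does not converge.

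The cost is a slightly longer model specification. No new data or change of design is needed.
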